#### Phase IV: randomized controlled trial

2.3.4

This phase is a pragmatic randomised controlled design to assess the effectiveness of AI-assisted diagnosis in the real world. Clinicians will be assigned in a 1:1 ratio to either the control group (using standard clinical assessment protocols) or the AI model-assisted group. Allocation will be by block group randomisation, stratified by hospital level (urban vs. rural) and clinician experience level (resident, attending, chief) to ensure balanced representation in key subgroups.

The control group will rely exclusively on routine diagnostic workflows, while the model-assisted group will integrate AI outputs into their decision-making process and retain full authority to accept or reject recommendations. The primary outcome is the between-group AUC difference, with a ΔAUC greater than 0.15 defined as clinically significant, which is consistent with the U.S. Food and Drug Administration’s (FDA) benchmarks for diagnostic tools based on artificial intelligence or machine learning (AI/ML). The design simulates real-world clinical practice and quantifies the added value of AI in improving diagnostic accuracy while preserving clinician autonomy.

#### Phase V: prospective validation study

2.3.5

As Dai et al. illustrate the point, using prospective cohort data validation provides a better view of the model’s performance in the real world (24). This final phase evaluates the model’s real-world clinical utility during the 2025 influenza season. The AI model will be deployed in real time to analyze EHRs of newly admitted influenza patients across all 87 hospitals. Clinicians will receive model-generated predictions (such as risk scores, key contributing factors) within 2 h of case entry via a secure, institution-specific dashboard.

Data collection will capture:

Clinician actions: Initial diagnosis (pre-model assessment), final diagnosis (post-model review), and time-to-decision (minutes from case entry to diagnosis).Model performance: Concordance between model predictions and ground truth (severe influenza confirmed by an independent adjudication panel).

This prospective design validates the model’s operational feasibility, diagnostic timeliness, and accuracy in dynamic clinical environments, providing critical evidence for scalability and regulatory approval.

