#### Phase II: external validation-comparative study

2.3.2

The goal of the second phase of the task was to comparatively confirm the diagnostic accuracy of the additional diagnostic assessment using the AI models built in the first phase to assist clinicians in diagnostic assessment. We categorised clinicians into residents, attending physicians and chief physicians according to their experience level. We asked clinicians in the control group to independently judge these influenza cases without the assistance of the AI model; while clinicians in the experimental group did the diagnostic assessment of these influenza cases with the assistance of the AI model. Under this comparison, the metrics of AUC, sensitivity, specificity, and diagnostic consumption time are what are used to initially evaluate the performance of the AI model. Imagine the exciting news that an AI model-assisted clinician can complete a diagnostic assessment with 95% accuracy in just 10 minutes. This dual assessment framework quantifies the added value of AI models in the real world.

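### Phase V is said to validate diagnostic timeliness, but its only timing measure cannot show that the model speeds recognition of severe influenza

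*Protocol article*

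**What the plan says.** Section 2.3.5 (Phase V) states: "The AI model will be deployed in real time to analyze EHRs of newly admitted influenza patients across all 87 hospitals". Predictions reach the clinician "within 2 h of case entry via a secure, institution-specific dashboard". The clinician actions to be captured are "Initial diagnosis (pre-model assessment), final diagnosis (post-model review"), followed by "time-to-decision (minutes from case entry to diagnosis"). The section names no group working without the model and no historical comparison. It concludes: "This prospective design validates the model’s operational feasibility, diagnostic timeliness, and accuracy in dynamic clinical environments", and offers this as evidence for scaling up and for regulatory approval.

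Timing also appears in section 2.3.2 (Phase II), where an unassisted control group is compared with an assisted group on "the metrics of AUC, sensitivity, specificity, and diagnostic consumption time". Section 2.7.2 places Phases I and II in the retrospective part of data collection, using records from 2019 to 2024.

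**The concern.** The stated aim of the study is early diagnosis, and Phase V is its real-world test. To say that a tool's timeliness has been validated, a design must be able to separate a tool that brings recognition forward from one that does not. That needs either a measure the tool can shorten or a comparator without the tool. Phase V appears to have neither, yet its result is offered to support deployment and approval.

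What is at stake is one stated conclusion of Phase V. Time-to-decision is not a primary or secondary outcome (sections 2.4.1, 2.4.2, 2.8.1 and 2.8.2), is not among the hypotheses in the Introduction, and does not enter the sample size (section 2.5.1).

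**Working it through.** The plan gives no effect size, standard deviation or power for time-to-decision, so there is no figure to reproduce. The check is structural, with a simulation for scale.

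**Inputs from section 2.3.5.** The pre-model diagnosis precedes the post-model one. Delivery takes at most 2 h (120 min), which is a ceiling and not a fixed time. All hospitals have the model.

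**Notation, in minutes from case entry.** T = time of the initial diagnosis; D = time the output is delivered, 0 ≤ D ≤ 120; R = time spent reviewing the output, R > 0; F = time of the final diagnosis.

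**Reading 1: the clock stops at the initial diagnosis.** The measure is T. It is complete before the model is seen, so it carries no model effect.

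**Reading 2: the clock stops at the final diagnosis.** The final diagnosis needs both the initial diagnosis and the output, so

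F = max(T, D) + R, and F − T = max(0, D − T) + R > 0.

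The accuracy of the model does not appear in this expression. The model can act on F only through R, and R only adds time. A perfect model and a useless one with the same delivery and review times give the same F.

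**Scale.** All of the following values are assumed, because the plan gives none: T lognormal with log-SD 0.6 and median 10, 30, 60 or 120 min; D = 1 min, uniform on 0 to 120 min, or 120 min; R = 1 or 5 min; 200,000 simulated cases. Mean of F − T in minutes, for R = 1:

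| Median T | D = 1 | D uniform 0–120 | D = 120 |
|---|---|---|---|
| 10 | 1.0 | 49.9 | 109.1 |
| 30 | 1.0 | 32.7 | 85.4 |
| 60 | 1.0 | 17.4 | 55.1 |
| 120 | 1.0 | 5.8 | 21.6 |

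With R = 5 each entry rises by 4 min, so the range over all scenarios is 1.0 to 109.1 + 4 = 113.1 min. The share of cases with F earlier than T was 0.000 in every scenario, as the formula requires.

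**How far the design determines F.** With D = 1, F follows the clinician's own time: its correlation with T is 1.00, and its SD runs from 7.9 min (median T = 10) to 94.8 min (median T = 120). With D = 120 and median T = 10, F is about 121 to 125 min with almost no spread. Delivery dominates only when it is late relative to T.

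**The comparator.** T is an unassisted time, but it is the time of a first call, right or wrong. The quantity needed is when a clinician without the model would have reached the correct severe call. With the model live at every site, that is not observed.

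**The case against.** The strongest reply is that section 2.3.5 promises no reduction in time. Timeliness stands beside operational feasibility in a deployment phase, and elapsed minutes under live use can fairly describe whether decisions are reached promptly. The comparative question is asked in Phase II, which has a control group. Which diagnosis ends the interval is an operational detail that a condensed article may leave to the full protocol. Much of this stands: the minutes are useful as description, and the undefined end-point alone would not be a point. What does not stand is the word validates, attached to the model's timeliness and offered for regulatory approval. Neither end-point supports it, so a fuller definition elsewhere would not rescue it.

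Three stronger readings are tempting, and the documents do not support them.

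- A reader might infer that time-to-decision is fixed by the sequence and the 2-hour window. It is bounded below, not fixed: 2 h is a ceiling, and the time still varies with clinician, case and actual delivery.
- A reader might infer a guaranteed apparent delay caused by the model. That needs a test of final against initial time in the same case, which the protocol never specifies. Any two-step record has its second step later. Where the initial call was wrong, a later correct one is not a delay.
- A reader might put the delay at about 50 min, taking an initial diagnosis at 10 min and uniform delivery: (10 × 10 + (120² − 10²)/2)/120 = 60.4 min, less 10. But the 10 minutes in section 2.3.2 is a hoped-for time for an assisted assessment, not an unassisted one, and uniform delivery is an assumption. The range above is too wide for one figure to mean much.

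**Conclusion.** The point holds in a limited form. Time-to-decision in Phase V can describe workflow under deployment. It cannot show that the model brings recognition of severe influenza forward, because of the pre-then-post order, the absence of an unassisted comparator, and an interval that is uninformative about speed whichever diagnosis ends it. This follows from what section 2.3.5 states and does not depend on the simulated values, which only show that the gap between initial and final diagnosis could lie anywhere from about 1 to 113 min. It does assume that the initial diagnosis is recorded before the output is viewed, as the section's labels imply.

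The weight is moderate: a stated Phase V conclusion is unsupported by its own design, but no primary or secondary test is affected.

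**What to change.** - In section 2.3.5, remove diagnostic timeliness from what Phase V validates, or restate it as descriptive workflow time under deployment.
- Time-stamp the initial diagnosis, the dashboard delivery and the final diagnosis separately, and say which interval each reported time refers to. Report delivery latency and review time as feasibility measures.
- Limit any assisted-versus-unassisted timing claim to case-reading time in the concurrent Phase II comparison, and say that its cases are retrospective, so it does not speak to timeliness at the bedside.
- Optionally, report lead time from the first correct severe call (initial or final) to the adjudicated event as a descriptive measure. It exists only for severe cases and also lacks an unassisted comparator, so it should not be presented as a model effect.

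The cost is a change of wording and the use of system time stamps from the dashboard and the health record; no extra patients are needed. The price is a narrower timing claim for Phase V.

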#### Exclusion criteria for patients

2.2.2

Co-infection with other respiratory pathogens confirmed by multiplex polymerase chain reaction (PCR);Critical illness unrelated to influenza at enrollment;Incomplete baseline data (such as missing symptom onset date, laboratory results).

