#### Calculation rationale

2.5.1

The sample size was determined based on the primary outcome (AUC comparison between model-assisted and clinician-only diagnoses) using a two-group superiority design. Key parameters were derived from prior studies on AI diagnostic tools (31, 32):

Expected effect size: ΔAUC = 0.15 (clinically meaningful improvement).

Type I error (*α*): 0.05 (two-tailed).

Power (1-*β*): 0.95.

Attrition rate: 20% adjustment for patient dropout or incomplete data.

The minimum sample size for AUC comparison was calculated using the following formula (33):

$$n=\frac{{\left(Z_{1-\alpha /2}+Z_{1-\beta }\right)}^{2}\times [\mathrm{AU}C_{1}(1-\mathrm{AU}C_{1})+\mathrm{AU}C_{2}(1-\mathrm{AU}C_{2})]}{{\left(\mathrm{AU}C_{1}-\mathrm{AU}C_{2}\right)}^{2}}$$

Where:

$\mathrm{AU}C_{1}$
 (model-assisted): 0.85 (34).

$\mathrm{AU}C_{2}$
 (clinician-only): 0.70 (null hypothesis).

$Z_{1-\alpha /2}$
= 1.96, 
$Z_{1-\beta }$
= 1.645.

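### The exclusion for incomplete baseline data has no phase limit, so as written it also applies to Phase V and can overstate the feasibility that Phase V sets out to show

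*Protocol article*

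**What the plan says.** Section 2.3.5 describes the Phase V population broadly: "The AI model will be deployed in real time to analyze EHRs of newly admitted influenza patients across all 87 hospitals". Clinicians are to receive predictions "within 2 h of case entry via a secure, institution-specific dashboard". The section concludes that the design validates "operational feasibility, diagnostic timeliness, and accuracy in dynamic clinical environments" and offers this as evidence for scaling up and for regulators.

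Two kinds of data are to be captured in Phase V. For clinicians they are "Initial diagnosis (pre-model assessment), final diagnosis (post-model review), and time-to-decision (minutes from case entry to diagnosis"). For the model it is "Concordance between model predictions and ground truth". No item counts patients who were excluded, never scored or scored late.

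Section 2.2.2 lists as a patient exclusion "Incomplete baseline data (such as missing symptom onset date, laboratory results"). It names no phase. Section 2.2 plainly covers prospective patients too: 2.2.1 requires written consent, and 2.5.3 counts retrospective and 2025 patients in one enrolled total. Laboratory and imaging findings are among the model's data categories (2.3.1).

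Other sections assume that incomplete records stay in. Sections 2.4.4, 2.7.4 and 2.8.4 impute remaining gaps, 2.8.5 compares results with and without imputation, and 2.5.1 makes a "20% adjustment for patient dropout or incomplete data".

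**The concern.** An important way for a live record-based tool to fail is that an input is missing when the score is due. A feasibility study has to count those patients. If they are removed at eligibility, the feasibility result is conditional on the data being there, which is part of what Phase V is meant to test. Accuracy is affected in the same way: concordance can be computed only where a prediction exists, so it would describe patients with complete records and not the admissions at all 87 hospitals.

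This cannot be left to a later analysis plan, because an analysis cannot recover patients who were never enrolled. In Phase IV, which 2.3.4 calls pragmatic, the same rule narrows the result to patients with complete data, although clinicians must also decide on the others.

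**Working it through.** **1. The sections side by side**

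- 2.2.2 removes patients. It acts at eligibility, in every phase, and names laboratory results. It does not say at what time completeness is judged.
- 2.4.4, 2.7.4 and 2.8.4 remove variables (above 20% missing, or categorical variables not below 10%) and impute the rest. They act on patients already in the data set.
- 2.8.5 plans a complete-case analysis as a contrast to the imputed one. If 2.2.2 were applied strictly to baseline items, the two would hardly differ on those items.
- 2.7.4 makes some fields mandatory. Its examples are viral subtype and symptom onset date; laboratory results are not among them.
- No section exempts Phase V from 2.2.2.

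So the sections conflict, and the one that decides who enters Phase V is 2.2.2.

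**2. Size of the effect on feasibility**

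The plan states no feasibility figure, so there is none to reproduce. Let m be the share of otherwise eligible patients with incomplete baseline data, c the share scored among complete records, and u the share scored among incomplete records.

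- Share scored among all patients: (1−m)×c + m×u
- Share reported after the exclusion: c
- Overstatement: c − [(1−m)×c + m×u] = m×(c−u)

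None of m, c and u is in the documents. For illustration, assume c = 98%:

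| m | All patients, u = 0 | Overstated by | All patients, u = 50% | Overstated by |
|---|---|---|---|---|
| 5% | 93.1% | 4.9 points | 95.6% | 2.4 points |
| 10% | 88.2% | 9.8 points | 93.2% | 4.8 points |
| 20% | 78.4% | 19.6 points | 88.4% | 9.6 points |
| 30% | 68.6% | 29.4 points | 83.6% | 14.4 points |

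For example, with m = 20% and u = 0: 0.80×98% + 0.20×0% = 78.4%, and 98% − 78.4% = 19.6 points. With u = 98% the overstatement is zero for every m.

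The 20% in 2.5.1 is the only figure in the protocol tied to incomplete data. It combines dropout with incomplete data, so it is not an estimate of m.

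**3. Phase IV**

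The exclusion is a baseline rule that applies alike to both arms. It changes the population to which the AUC difference refers. Nothing in the protocol shows that it biases the comparison between arms.

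**The case against.** The strongest reply is that the protocol does not clearly delete incomplete records. It imputes gaps, plans a complete-case comparison and allows for incomplete data in the sample size, so the authors evidently expected such patients among those enrolled. This stands in part: the fault is a conflict between sections, not a clear instruction to drop every incomplete record. It does not dispose of the point, because imputation handles patients already enrolled and 2.2.2 acts before that.

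A second reply is that 2.2.2 is not tied to the 2 h window. A patient whose laboratory result arrives after 2 h can have a late score and complete baseline data, and so stay in. Technical failures of the dashboard would not trigger the exclusion either. This also stands. A reader might infer that measured feasibility must come out near 100% whatever happens; the documents do not support that. They also do not say that a missing input always prevents a score.

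A reader might further infer that counting unscored patients would push the AUC difference below the 0.15 threshold. Such a calculation starts at exactly 0.15 and assumes no benefit in unscored patients, so any unscored share falls short by assumption. It is no evidence of what would happen.

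Last, feasibility is not a listed outcome in 2.4, and a condensed article may leave denominators to a fuller document. That is fair for the analysis details, but not for an eligibility rule that the article states itself.

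**Conclusion.** The point holds in a limited form. As written, 2.2.2 applies to Phase V, conflicts with the missing-data sections, and removes patients who are likely feasibility failures. Feasibility is overstated wherever incomplete records are scored less often than complete ones. The direction is likely; the size cannot be derived from the documents. The illustrative range of 0 to about 29 points rests on assumed values: c = 98%, m from 5% to 30%, and u from 0 to 98%.

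The effect on accuracy and on the AUC difference is less certain than the effect on feasibility, and no figure is claimed for it. For Phase IV the consequence is narrower generalisability, not a demonstrated bias. This should be corrected before prospective enrolment.

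**What to change.** Reconcile 2.2.2 with 2.3.5, 2.4.4, 2.7.4, 2.8.4 and 2.8.5 as follows:

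- State that the exclusion for incomplete baseline data does not apply to patients enrolled prospectively in Phases IV and V. Keep every consented patient who meets the other criteria.
- Analyse the clinician's diagnosis as made, whether or not a score was delivered; in Phase IV, in the allocated arm.
- Report the share of patients with a score within 2 h, and the shares scored late and never scored, each with a 95% confidence interval and with all these patients in the denominator.
- Keep the complete-data analysis as secondary.

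The cost is a sentence on eligibility and a few lines on the analysis population and reporting. No new patient procedure is needed, though the delivery time of each score has to be logged. The downside is that feasibility, AUC and the AUC difference may look less favourable than among patients with complete data.

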### Outcomes

2.4

#### Primary outcome

2.4.1

As the ultimate goal of this clinical trial is to create highly accurate AI models. Therefore the primary outcome metric was set as the area under the curve (AUC) (25). The AUC quantifies the discriminatory ability of the AI model so that it can distinguish patients who may develop severe influenza from those who will not. Since calculating the AUC requires the use of sensitivity, specificity, true positive rate, true negative rate, false positive rate, and false negative rate, more details describing these results can be found in our separate studies (16, 20).

To account for differences in diagnostic assessments after multiple clinicians read the cases, we planned to use the Dorfman-Berbaum-Metz (DBM) method. The DBM adjusts for differences in diagnostic assessments by clinicians so that AUC difference values between the two groups can be estimated (22). ROC curves were calculated using the pROC (version 1.18.0) software package (28). The AUC values as well as their 95% confidence intervals will then be calculated using MRMCaov (version 0.2.1) (27). For differences between the experimental and control groups, we expected to use the Mann-Whitney U test (29). Clinically significant improvement was defined as an AUC difference between the experimental and control groups greater than 0.15. The null hypothesis here is that the AUC difference is less than 0.7, and the AI model has no discriminatory power. Our method of using AUC to set thresholds not only follows statistical patterns, but is also highly compliant with the criteria for the development of AI-driven diagnostic tools.

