#### Phase overview

2.1.4

The study comprises five sequential phases, which is based on the multiple nesting approach used in [name]’s past methods (16–20).

Model development: retrospective data (2019–2024) from 87 hospitals for training and internal validation.External validation-comparative study: benchmarking model performance against clinician diagnoses.Multi-reader, multi-case validation: assessing inter-physician variability with/without model assistance.Randomized controlled trial: evaluating real-time diagnostic accuracy in a clinician-AI collaborative setting.Prospective validation: real-world testing during the 2025 influenza season.

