#### Primary outcome analysis

2.8.1

The AUC will serve as the primary metric to evaluate the diagnostic accuracy of the AI model. To account for variability inherent in multi-reader, multi-case study designs, the DBM method will be employed, which adjusts for differences in clinician interpretations and case complexity. Analyses will be conducted using the MRMCaov (v0.2.1) and pROC (v1.18.0) packages in R, generating AUC values with 95% confidence intervals (CIs) derived from non-parametric bootstrapping (1,000 iterations). A clinically significant improvement is predefined as a ΔAUC more than 0.15 between the model-assisted and control groups, with the null hypothesis assuming no discriminative capacity (AUC less than 0.70, equivalent to random guessing). This approach ensures robust statistical inference while addressing real-world diagnostic variability across clinicians and settings. Hyperparameter optimization was conducted via Bayesian optimization with 5-fold cross-validation, prioritizing AUC on the validation set.

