#### Secondary outcomes analysis

2.8.2

Secondary endpoints include diagnostic sensitivity and specificity, calculated using the Clopper-Pearson exact method for binomial proportions to determine the model’s and clinicians’ ability to correctly identify true positive and true negative cases, respectively. Differences between clinician and model performance will be assessed via the Mann–Whitney U test, a non-parametric method suitable for skewed distributions. Positive and negative predictive values (PPV/NPV) will be adjusted for influenza prevalence using Bayes’ theorem and reported with 95% confidence intervals to reflect their clinical utility in real-world settings. The misdiagnosis rate, defined as the sum of false positives and false negatives per 100 diagnoses, will be analyzed using an independent samples t-test (if normally distributed) or Wilcoxon rank-sum test (for non-normal data), quantifying the model’s impact on reducing diagnostic errors. These metrics collectively evaluate the model’s precision, reliability, and practical value in augmenting clinical decision-making.

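### Sections 2.4.1 and 2.8.1 define the primary AUC and its null by the AI model's own accuracy, while Phase IV, the sizing and the 0.15 criterion concern the difference between assisted and control clinicians

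*Protocol article*

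**What the plan says.** **The model's own AUC.** Section 2.4.1 (Primary outcome) derives the endpoint from the aim of building accurate AI models and says "The AUC quantifies the discriminatory ability of the AI model". Its null combines an AUC difference below 0.7 with the model lacking discriminatory power. Section 2.8.1 (Primary outcome analysis) says "The AUC will serve as the primary metric to evaluate the diagnostic accuracy of the AI model" and continues "with the null hypothesis assuming no discriminative capacity (AUC less than 0.70, equivalent to random guessing".

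**The difference between clinician groups.** Section 2.3.4 (Phase IV) says "The primary outcome is the between-group AUC difference" for clinicians randomised 1:1. Section 2.5.1 (Calculation rationale) names the primary outcome as "AUC comparison between model-assisted and clinician-only diagnoses". The criterion of more than 0.15 in 2.4.1 and 2.8.1 is also set between the experimental (model-assisted) and control groups.

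**Related places.** The hypothesis in the Introduction attaches a gain above 0.15 to the model against physician-only assessment. Section 2.1.4 (Phase overview) describes Phase II as "benchmarking model performance against clinician diagnoses". Section 2.3.2 describes the same phase as a comparison of assisted with unassisted clinicians: "clinicians in the experimental group did the diagnostic assessment of these influenza cases with the assistance of the AI model".

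**The concern.** A model's AUC comes from the model's scores. It involves no clinician behaviour and no randomised contrast. The Phase IV difference comes from clinicians' diagnoses with and without the tool, and section 2.6.3 leaves those clinicians free to accept, change or reject what the tool shows. A high value of the first does not establish the second.

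The two governing sections contain both: a definition and a null about the model, and a success threshold about the arms. If the results disagree, the protocol does not say which decides the primary question. A rejected null about the model could then be reported as the trial's primary result, although the randomised comparison had missed its own criterion.

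**Working it through.** **1. The passages side by side**

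| Place | Whose AUC | Null or threshold |
|---|---|---|
| Introduction, hypothesis | Model vs physician-only | Above 0.15 |
| 2.1.4, Phase II | Model vs clinicians | none |
| 2.3.2, Phase II | Assisted vs unassisted clinicians | none |
| 2.3.4, Phase IV | Between randomised clinician groups | Above 0.15 |
| 2.4.1, definition and null | The AI model (the null also mentions a difference) | Difference below 0.7 and no model discrimination |
| 2.4.1, criterion | Experimental vs control | Above 0.15 |
| 2.5.1 | Assisted vs clinician-only | 0.85 vs 0.70 |
| 2.8.1, definition and null | The AI model | A single AUC below 0.70 |
| 2.8.1, criterion | Model-assisted vs control | Above 0.15 |

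No sentence in 2.4.1 or 2.8.1 ranks the two quantities or assigns them to phases.

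**2. The plan's own figure.** The formula in 2.5.1 gives (1.96 + 1.645)² × (0.85×0.15 + 0.70×0.30) / 0.15² = 12.996 × 0.3375 / 0.0225 = 194.9, so 195 per group. Section 2.5.2 states 145. That discrepancy is a separate matter and nothing below depends on it. What matters here is that the calculation is for a difference between two groups, not for one model's AUC.

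**3. Can the two definitions disagree? The model-based null.** Inputs: 348 patients (2.5.3), null 0.70 (2.8.1), model AUC A = 0.85 (assumed; 2.5.1 gives 0.85 for assisted clinicians), severe share 10% to 50% (assumed). Hanley-McNeil variance:

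SE² = [A(1−A) + (n₁−1)(Q₁−A²) + (n₀−1)(Q₂−A²)] / (n₁n₀), with Q₁ = A/(2−A) = 0.7391, Q₂ = 2A²/(1+A) = 0.7811 and A² = 0.7225.

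- 10% severe (35 and 313): SE² = (0.1275 + 34×0.0166 + 312×0.0586)/10,955 = 0.00173, SE 0.0416, lower limit 0.85 − 1.96×0.0416 = 0.77.
- 50% severe (174 and 174): SE² = (0.1275 + 173×0.0752)/30,276 = 0.00043, SE 0.0208, lower limit 0.81.

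Both limits lie above 0.70, so the model-based null is rejected.

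**4. The between-arm difference with the same model.** Inputs: unaided clinicians 0.70 (2.5.1), binormal scores with unit variance. Separations are d = √2·Φ⁻¹(AUC): 1.466 for the model and 0.742 for clinicians.

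*Uptake.* Suppose clinicians use the model's score in a share p of cases and keep their own rating otherwise. With both scales centred on a common midpoint, a pair in which one case is rated by the model and the other by the clinician is ordered correctly with probability Φ[(1.466 + 0.742)/(2√2)] = 0.782. Then assisted AUC = 0.85p² + 0.70(1−p)² + 2p(1−p)×0.782.

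- p = 0.25: 0.053 + 0.394 + 0.293 = 0.74, gain 0.04
- p = 0.50: 0.213 + 0.175 + 0.391 = 0.78, gain 0.08
- p = 0.75: 0.478 + 0.044 + 0.293 = 0.82, gain 0.12 (0.11 if the two scales are aligned on the non-severe cases instead)

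*Equal averaging*, conditional correlation 0.3 (assumed): Φ[2.207/√(2×2.6)] = Φ(0.968) = 0.83, gain 0.13.

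All four gains are below 0.15. The model's own margin over unaided clinicians is 0.85 − 0.70 = 0.15.

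**5. Limit of the illustration.** With an optimally weighted combination under the same assumptions, assisted AUC is about 0.856. The gain then just exceeds 0.15 and the two definitions agree. The example shows that they can disagree, not how often.

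**The case against.** The strongest reply is that the operative text already points one way. Sections 2.3.4, 2.4.1 and 2.8.1 all tie the 0.15 criterion to model-assisted against control groups. Sections 2.6.1 and 2.6.3 define no standalone-model arm. The sizing in 2.5.1 is for assisted against clinician-only diagnoses. The Dorfman-Berbaum-Metz method is introduced to handle variation among clinicians reading the cases, which points to clinicians' ratings. All of this stands.

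A reader might therefore infer too much in two respects. The first is that the 0.15 success rule can be met by the model's own AUC. The three operative sections do not allow that. Only the Introduction's hypothesis, and the abstract's expectation that the model will outperform clinical assessment, read that way. The second is that the protocol nowhere indicates whose ratings form the ROC curve. The choice of a reader-based method shows that it does.

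Section 2.8.2 does say "Differences between clinician and model performance will be assessed", but it covers secondary outcomes, where such a comparison belongs, so it is not part of the conflict.

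The reply does not remove the opening definitions in 2.4.1 and 2.8.1, or the nulls there that refer to the model's discrimination. Nor is this detail that can be left to an analysis plan: such a plan would have to contradict one of the protocol's own statements.

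**Conclusion.** The concern holds in a limited form. Sections 2.4.1 and 2.8.1 define the primary AUC, and state a null, in terms of the AI model. Section 2.3.4, section 2.5.1 and the 0.15 criterion make the primary outcome a difference between clinician groups. The text does not rank them, so the model-based null could be rejected while the randomised arms differ by less than 0.15. The Phase II descriptions in 2.1.4 and 2.3.2 conflict in the same way.

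That the definitions conflict rests on the text alone. The size of the gap does not. With a 0.85 model and 0.70 clinicians, the assisted gain runs from about 0.04 at 25% uptake to about 0.13 with equal averaging, against 0.15 for the model alone, and it can close entirely. Uptake, correlation, the binormal form and the severe share are assumptions, and the calculation ignores clustering by reader and hospital.

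**What to change.** - In 2.4.1 and 2.8.1, state one primary endpoint: the Phase IV difference in AUC between the randomised arms, model-assisted minus control, computed from the clinicians' recorded ratings.
- State the null and the 0.15 criterion for that difference only, and remove the null about the model's discrimination from the primary outcome.
- List the model's own AUC, and the model against unaided clinicians, as named secondary outcomes for the other phases.
- Reword the Introduction's hypothesis as assisted against unassisted clinicians, and bring the Phase II line in 2.1.4 into agreement with 2.3.2.

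The cost is protocol wording. No data are lost and the model's AUC is still reported. The downside for the sponsor is that the model's own AUC can no longer support the primary claim.
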